### Cognitive interviews

All participants taking part in focus groups will be sent a copy of the third version of the questionnaire (via email or post) and invited to take part in follow-up interviews over the telephone. The interviews will follow a semistructured interview format. Techniques, such as ‘thinking aloud’ and verbal probing, will be used to ensure that items are correctly understood, and to identify problems with wording and/or difficulties with response options. In order to reduce participant burden, participants will be encouraged to focus on items which they identified as being particularly difficult or easy to understand, or those which they feel could be reworded more effectively. It is anticipated that each interview will last between 20 and 30 min. Based on this feedback, a β version of the questionnaire will be finalised. This will complete the development stage of the study.

## Phase 2: Psychometric evaluation of the ACB

### Main sample

To establish the initial psychometric properties of the questionnaire, 200 participants will be recruited to complete the ACB, in addition to other standardised measures of concerning behaviour (table 1). The questionnaire battery will also incorporate a treatment report form detailing current medication/therapy/intervention status. The treatment report form will be completed by parent/carers of children with ASD, and adults with ASD will be asked to report on their own treatment. Where adults are unable to report on their own treatment, their parent/carer/relative/partner will be asked to complete the treatment report form. The Social Communication Questionnaire^24^ will be completed by parents/caregivers at study entry for characterisation of the study sample.

**Table 1 BMJOPEN2015010693TB1:** Gold standard instruments to be administered to participants in the main sample during the validation stage of the study

		Administered to							
Measure	Key psychometric information	Child with ASD	Young person with ASD	Adult with ASD	Parent/carer of child with ASD	Parent/carer/partner of adult with ASD	Teacher	Employer	Clinician/researcher
Social Communication Questionnaire (SCQ) Lifetime Version^24^	The SCQ shows strong discrimination between ASD and non-ASD cases (sensitivity 0.88, specificity 0.72^32^). Satisfactory internal reliability of the whole scale has been reported (α=0.90^33^).				**X**	**X**			
Child Behaviour Checklist (CBCL) Parent Report^28^	The Achenbach Manual reports acceptable internal reliability of the scales with α values ranging from α=0.72 for the Anxiety Problems subscale to α=0.97 for the Total Problems subscale.^28^ Eight-day test–retest reliability is acceptable; correlations ranging from r=0.80 for the Anxiety Problems subscale to r=0.94 for the Total Problems subscale.^28^				**X**				
Child Behaviour Checklist (CBCL) Teacher Report^28^	Acceptable internal reliability (α values range from α=0.72 for Somatic Complaints and Thought Problems subscales to α=0.95 for Attention Problems, Rule Breaking Behaviour and Aggressive Behaviour subscales^28^). Sixteen-day test–retest values range from r=0.6 for the Withdrawn/Depressed subscale to r=0.96 for the inattention items.^28^						**X**		
Youth Self-Report (YSR)^28^	Internal reliability values range from α=0.67 for the Anxiety subscale to α=0.95 for the Total Problems scale.^28^ Test–retest (8 days) correlations range from r=0.67 for the Withdrawn/Depressed subscale to r=0.89 for the Externalising Behaviour Subscale.^28^	**X**	**X**						
Adult Behaviour Checklist (ABCL)^29^	Internal reliability coefficients are moderate to strong (α=0.67 for Adaptive Functioning—Friends subscale to α=0.97 for the Total Problems subscale).^29^ Test–retest reliability is acceptable (r=0.73 for the Withdrawn subscale to r=0.94 for Substance Use subscale).^29^					**X**		**X**	
Adult Self-Report (ASR)^29^	Internal reliability estimates are moderate to strong ranging, from α=0.51 for the Adaptive Functioning—Education subscale and Thought Problems subscale to α=0.97 for the Total Problems subscale. Test–retest correlation coefficients range from r=0.71 for the Adaptive Functioning—Job subscale to r=0.99 for the Substance Use—Drugs subscale.^29^			**X**					
Aberrant Behaviour Checklist (ABC)^30^	This scale has 5 subscales with α coefficients ranging between 0.86 for Inappropriate Speech to 0.94 for Hyperactivity.^30^ The 4-week test–retest for all of the subscales are between r=0.96–0.98.^30^				**X**	**X**	**X**	**X**	
The Modified Overt Aggression Scale^34^ ^35^	The inter-rater reliability of this instrument has been assessed in a sample of adults with ID (ICC=0.93;^36^).				**X**	**X**	**X**	**X**	
Clinical Global Impressions Scale (CGI)	The CGI correlates well with well-known efficacy scales.^37^ ^38^ The CGI is used in many treatment trials.^39^								**X**
Home Situations Questionnaire (HSQ)- Modified for ASD^40^	Good internal reliability for both subscales (α=0.89 for Demand Specific subscale and α=0.84 for Socially Inflexible subscale).^40^ Test–retest reliability has been shown to be r=0.57 for the Socially Inflexible subscale, r=0.58 for the Demand Specific subscale and r=0.57 for Total Score.^40^				**X**				
Treatment report form	Non-validated questionnaire developed for this study.			**X**	**X**	**X***			
Approximate total administration time (min)		55 (+20 min for ACB)	55 (+20 min for ACB)	72 (+20 min for ACB)	82 (+20 min for ACB)	77 (+20 min for ACB)	55 (+20 min for ACB)	40 (+20 min for ACB)	12 (+20 min for ACB)

*To be completed when adults with ASD are unable to report on their own treatment.

ACB, Assessment of Concerning Behaviour Scale; ASD, Autism Spectrum Disorders; ICC, Intraclass Correlation Coefficient.

Participants’ questionnaire battery will be presented in HealthTracker™, a web-based platform for online completion (www.healthtracker.co.uk) that is currently being used in two EU FP7 projects—the Suicidality: Treatment Occurring in Paediatrics (STOP study; http://www.stop-study.com) and the Managing the Link and Strengthening Transition from Child to Adult Mental Health Care (MILESTONE) project (http://www.milestone-transitionstudy.eu). HealthTracker™ has also been used in a previous questionnaire development and validation study.^25^ The web-based questionnaires will follow the principles of data protection, security levels for health data, have an audit trail and Good Clinical Practice compliance. Participants will be given a unique ID number and log-in information, and will be asked to complete the questionnaires independently. All participants, including those with literacy issues, will have the option of going through the questionnaires over the phone with a member of the research team. Participants will also be able to complete paper versions of the questionnaires if requested. Questionnaire completion should not take longer than approximately 60 min for adults and 40 min for children.

Participant medical records will be accessed to validate the ACB against details of diagnoses obtained from patient case notes as well as against Development and Well-being Assessment (DAWBA^26^) diagnoses, IQ and treatment/medication status if they are available in case notes. Consent will be obtained to access medical notes. For children recruited via schools, the research team will also request details about IQ, educational attainment and diagnoses from school records. Parental consent will be obtained to do this. Where measures of IQ are not available from participant medical/school records, a brief measure of IQ will be collected by the research team (see table 1).

All participants will be asked to complete the questionnaire battery twice: at study entry and again between 4 and 6 months after initial completion. This is to allow for analysis of the stability of the questionnaire. Based on clinical experience, 4–6 months was chosen as an appropriate period of time in which one would anticipate change in symptoms (eg, in relation to treatment response). Information on treatment, diagnoses and other relevant information will be gleaned from medical records in order to estimate when change of scores would be expected.

Approximately 50 participants, along with their parent/carer/relative/partner, teacher/employer and clinician will be asked to complete the ACB and gold standard questionnaires (see table 1) again, 1 week after their initial completion, to provide a measure of test–retest reliability. However, interim analyses will be conducted after 25 participants have completed the measure at 1 week. If a statistically significant correlation is evident, no further participants will be asked to complete measures again after 1 week. Since some of the items measured in the ACB are likely to be related to changeable constructs, a priori decisions will be made about items in the ACB that are expected to remain stable over 1 week.

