###### Test–retest reliability

To assess test–retest reliability, intraclass correlation coefficients will be calculated on subscale and total scores which are expected to remain stable. As this is an exploratory study, weighted Cohen's κ values will be also calculated to assess test–retest reliability at the item level. Coefficients will be established separately for children and adults, and also for parent/carer/relative/partner, teacher/employer and clinician reports on samples of approximately 50 questionnaires completed approximately 1 week after initial completion. For scores that are expected to remain stable, we anticipate a high intraclass correlation of 0.80, for which a sample of 37 would provide a 95% CI of width 0.2. Intraclass correlation coefficients will also be calculated to assess the longer term stability of the measure 4–6 months after initial completion of the questionnaire.

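### The interim rule stops 1-week retesting at 25 participants on statistical significance, a bar of about r = 0.40, and so gives up the precision the plan itself sets for the test–retest ICC

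*Protocol article*

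**What the plan says.** Two parts of the protocol article bear on this.

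- **Phase 2, Main sample.** The retest sample is set first: "Approximately 50 participants, along with their parent/carer/relative/partner, teacher/employer and clinician will be asked to complete the ACB" and the comparison measures a second time, "again, 1 week after their initial completion, to provide a measure of test–retest reliability". It then adds that "interim analyses will be conducted after 25 participants have completed the measure at 1 week", followed by the stopping rule: "If a statistically significant correlation is evident, no further participants will be asked to complete measures again after 1 week". The rule gives no null value, significance level, type of correlation, score, informant version or age group.
- **Reliability, Test–retest reliability.** Here "intraclass correlation coefficients will be calculated on subscale and total scores which are expected to remain stable". The sample is justified by precision: "we anticipate a high intraclass correlation of 0.80, for which a sample of 37 would provide a 95% CI of width 0.2". On strata: "Coefficients will be established separately for children and adults, and also for parent/carer/relative/partner, teacher/employer and clinician reports", and this is to be done "on samples of approximately 50 questionnaires completed approximately 1 week after initial completion".

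The article does not link the stopping rule to the precision target.

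**The concern.** A significance test asks whether the retest correlation differs from zero. Two completions of the same questionnaire by the same person a week apart are almost certain to correlate above zero, so rejecting that null says little about whether reliability is adequate or well estimated. The analysis section asks a different question: how precisely an ICC near 0.80 can be estimated.

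The interim sample of 25 is below both the 37 and the roughly 50 that the article gives elsewhere. A significant result at that look fixes the final sample at 25. Test–retest reliability is a core property of an instrument intended for clinical use and as a trial outcome, and one-week retests that are not collected on time cannot be recovered later.

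**Working it through.** **Inputs.** From the protocol: anticipated ICC ρ = 0.80; 95% CI of total width w = 0.2; stated n = 37; interim n = 25; planned n about 50; two occasions, so k = 2. Assumed, because not stated: null correlation of zero and a two-sided 5% level.

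**1. The plan's own figure.** Bonett's formula for ICC precision is n = 8z²(1−ρ)²(1+(k−1)ρ)² / (k(k−1)w²) + 1.

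- 95%, k = 2: 8 × 3.8415 × 0.04 × 3.24 / (2 × 0.04) + 1 = 50.8, so 51. The stated 37 is not reproduced.
- 90%, k = 2: 36.06, so 37, an exact match.
- 95%, k = 3: 35.6, so 36.

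The 37 therefore fits a 90% interval, or nearly fits three occasions, but not the stated 95% level with two. The exact one-way F interval first falls below 0.2 at 54 pairs.

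**2. The bar set by the rule at n = 25.** Critical r = t/√(df + t²), with df = 23 and t = 2.069, is 2.069/√(23 + 4.279) = 0.396. The Fisher z 95% CI at that value is about 0.00 to 0.68. One-sided, the bar is 0.337. If the interim coefficient is an ICC tested against zero by F, the bar is about 0.38 two-sided or 0.33 one-sided, so the choice of coefficient hardly matters.

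**3. Chance of stopping at 25.** Simulated bivariate-normal samples of 25, one score, two-sided 5%:

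| True correlation | Probability of stopping |
|---|---|
| 0.3 | 31% |
| 0.4 | 52–53% |
| 0.5 | 75% |
| 0.6 | 91% |
| 0.7 | 98% |
| 0.8 | 99.9% |

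**4. 95% precision at ICC 0.80, k = 2.** Bonett width = √[8z²(1−ρ)²(1+ρ)² / (2(n−1))]. At n = 25 this is √(3.983/48) = 0.288. For the exact interval, F = 1.8/0.2 = 9. The lower limit uses 9/2.242 = 4.014, giving 3.014/5.014 = 0.601. The upper limit uses 9 × 2.257 = 20.32, giving 19.32/21.32 = 0.906. The width is 0.305.

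| Pairs | Bonett width | Exact F width |
|---|---|---|
| 12 | 0.425 | 0.476 |
| 13 | 0.407 | 0.453 |
| 25 | 0.288 | 0.305 |
| 37 | 0.235 | 0.245 |
| 50 | 0.202 | 0.208 |
| 51 | 0.200 | 0.205 |
| 54 | 0.194 | 0.199 |

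The width at 25 is about 1.5 times the target (0.305/0.2). The planned 50 comes close to the target for one coefficient. The rows for 12 and 13 apply only if the 25 divide evenly between children and adults, which the article does not say.

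**The case against.** The best case for the rule is burden. Table 1 puts the parent battery for a child at 82 minutes plus 20 for the ACB, and the article describes this work as exploratory. Sparing families a repeat is a fair aim, although the article does not give it as the reason. It supports having an early stop, but not one based on significance.

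Some stronger readings are tempting, and the document does not support them.

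- **Unreliable scores would be accepted.** The rule decides only whether more people are retested. ICCs and item-level weighted kappas are still calculated, and no pass mark is set for test–retest reliability. A low ICC would be visible, though imprecise.
- **Retesting stops whatever the reliability.** It does not: on one score it stops in 31% of samples at a true correlation of 0.3. The rule discriminates, at too low a bar. If any one of many scores or informants could trigger it, stopping would be more likely, but the article does not say so. Even ten independent tests of truly zero correlations give 1 − 0.95¹⁰ = 40%.
- **The rule uses a different coefficient from the analysis.** The word used is simply correlation, which could mean the ICC.
- **Each age group is left with 12 or 13 pairs.** That needs an even split of a single sample. The roughly 50 questionnaires in the analysis section could also be read as 50 per coefficient.
- **Subscales from the factor analysis will not exist at the interim.** Probably so, but a total score will, and subscale ICCs can be computed later from stored item responses.

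After these are set aside, the low bar and the conflict with the precision target remain.

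**Conclusion.** The point holds as a conflict between a stated rule and the plan's own precision target. It is sharpest in the scenario the plan expects: with a true ICC of 0.80 the rule ends retesting at 25 with probability 99.9%, leaving a 95% CI of roughly 0.60 to 0.91 instead of one 0.2 wide. If the 25 are shared evenly between children and adults, the width in each group is about 0.41 to 0.48.

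The stopping probabilities assume a null of zero, a two-sided 5% level, bivariate normality and a single score; a one-sided test lowers the bar further. The widths assume an observed ICC of 0.80. Separately, the stated 37 does not deliver a 95% width of 0.2 with two occasions, so comparing 25 with 37 understates the shortfall. Other reliability, validity and factor analyses are unaffected.

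**What to change.** 1. Delete the significance-based stop and retest the approximately 50 participants already planned. This costs one sentence and up to 25 further retests, with their questionnaire burden; all are already in the plan.
2. If an early stop is kept, base it on the width of the 95% CI for the total-score ICC, and name the informant version and age group to which it applies. At 25 pairs a width of 0.2 would be met only with a high observed ICC: by Bonett, 1 − ICC² = 0.2/0.80 = 0.25, so about 0.87.
3. Restate the precision figure. At ICC 0.80 with two occasions, a 95% width of 0.2 needs about 51 pairs per coefficient (54 by the exact interval); 37 pairs give about 0.235 to 0.245.
4. Say whether the approximately 50 is the total or the number per age group. If it is the total, about 25 per group under an even split, state a width of about 0.3 for each group. Holding 0.2 in both groups would take about 2 × 51 = 102 participants, which goes beyond the roughly 50 planned and is a real added cost.

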### Augmented sample for factor analysis

In order to permit a factor analysis of the ACB, we will then aim to augment the main sample with a further 150 children and 150 adults with ASD in addition to their parent/carer/relative/partner, teacher/employer and clinician, who will complete the ACB only. Attempts will be made to ensure that the augmented sample is comparable with the main sample on age, gender, IQ and recruitment source. Participants in the augmented sample will be asked to complete the ACB, in addition to providing demographic information. Similar to the main sample, the ACB will be presented to participants in HealthTracker™. Participants will only be required to complete the ACB once, after which, their involvement in the study will end.

#### Recruitment

Information sheets (and age-appropriate information sheets where relevant) will be provided for all participants. Written informed consent and assent (where appropriate) will be obtained from all participants taking part in either stage of the research project. The purpose of the study and issues surrounding consent and confidentiality will be outlined to participants before consent is obtained.

Where the research team has doubts about a person's capacity to consent, a capacity checklist will be completed with the participant. If a participant is unable to provide informed consent, consent for their participation will be gained from their legal guardian or a personal consultee, and assent will also be sought from the participant.

##### Phase 1 recruitment

Children (7–12 years), young people (13–18 years) and adults with ASD, parent/caregivers of individuals with ASD, and teachers and clinicians who work with individuals with ASD will be recruited. Owing to the group-based nature of the focus groups, adults lacking capacity to consent will not be able to partake in focus groups and will be excluded. Separate focus groups will be conducted with each group (children with ASD, young people with ASD, adults with ASD, parents/carers, teachers and clinicians). Approximately 3–8 participants will take part in each focus group. No more than 60 participants in total will take part in the instrument development stage of the research.

Participants with ASD, and parents of individuals with ASD, will be recruited from clinics within participating trusts that see people with ASD and related developmental disorders. The research team or clinicians involved in the patients’ usual care will invite individuals with ASD and parents of children with ASD to take part. Attempts will be made to recruit individuals with a range of concerning behaviours and intellectual abilities, through consultation with the clinician involved in the patient's usual care, and through recruitment from clinics specialising in different disorders associated with ASD. Furthermore, the sample will also consist of individuals recruited from non-clinical sources in order to include participants who have received a diagnosis but are not currently accessing clinical services. This will include recruitment from schools catering to a range of intellectual abilities and from community sources, such as support groups.

Clinicians who work with ASD in participating trusts will be invited to take part in focus groups and follow-up cognitive interviews. Teachers will be invited by contacting local autism-specialist schools in the London area via invitation letter to the head teacher.

Inclusion criteria
Children (aged 7+ years), young people and adults with ASD (via clinician/researcher invite).Parents/carers of children with ASD.Teachers working within autism specialist schools for children and young people in the London area.Clinicians who work within healthcare settings in participating trusts that see children and/or adults with ASD and associated developmental conditions.

Exclusion criteria
Participants who do not have a reasonable level of English; a reasonable level of English, will be required to engage in the focus group/cognitive interviews.Individuals with ASD who are not verbal will not be included in focus groups/interviews. However, carers, teachers and parents of that person may still take part in their respective groups if they wish.Adults lacking capacity to consent will not be included in focus groups/interviews.If children, young people, or adults with ASD are not able to (or expected to not be able to) partake in the focus groups, they will be excluded from the instrument development stage. Discussions with clinicians involved in the patient's usual care/caregivers/the patient themselves prior to consent will be used to explore the individual's ability to partake in focus groups, and the levels of distress it would potentially cause them.

##### Phase 2 recruitment

###### Main sample

Individuals with ASD (children, young people and adults) and their parents/caregivers/relatives/partners, teachers/employers and clinicians will be invited to take part (see below for inclusion criteria). Individuals with ASD will be recruited via clinician/researcher invite as well as via poster advertisements within healthcare and community settings, social media and websites for ASD support groups. Individuals with ASD will also be recruited from autism-specific schools and residential settings. Researchers will primarily be recruiting participants via clinics within participating trusts; the aim is to recruit approximately 75% via this method. This is to ensure access to medical notes for as many participants as possible. However, participants will not be excluded if they are not currently under the care of participating trusts. Parental consent will be obtained to request details about the child's IQ, educational attainment and diagnosis from school records.

Parents of children with ASD will be asked to provide details of their child's teacher and clinician, and will provide consent for the research team to contact them and invite them to complete the study questionnaires. Adults with ASD will be asked to provide details of another person who knows them well (either a parent/caregiver/relative/partner) who would be able to complete a questionnaire about them. Adults with ASD will also be asked to provide contact details for their clinician and their employer (if applicable and appropriate).

